### Adverse events

Adverse events or other unintended effects of trial interventions or trial conduct in the RCT will be collected, assessed, and reported in accordance with Norwegian legislation [30]. These possible events and effects will be reported in the trial outcomes. If the PU does not heal during the follow-up period, the participant will be invited to further follow-up also after the termination of the RCT.

### Intervention

In our previous feasibility study [11] one of the important factors regarding PU healing was that the follow-up was performed by a few dedicated homecare nurses, as this continuity resulted in a better overall overview of the follow-up. The feasibility study also showed the importance in using a simple, common description of the PU status and the plan for the further treatment. These principles will be continued for both groups in the RCT.

The location and grade of the PU, and comorbidities influencing the healing process, will lead to individualized follow-up for each participant. In case of adverse effects, or worsening of the PU, necessary therapeutic measures will be initiated to prevent further worsening of the condition. If needed, surgical treatment or inpatient care will be recommended. All adverse events and worsening of the condition will be recorded in the wound journal and in the report form. In case of bacterial infection of the PU, laboratory tests will be performed, and the participant and the general practitioner will be informed. The local caregivers will be informed with permission from the participant.

An interdisciplinary wound journal has been drafted to map current age, marital status, socioeconomic status, lifestyle factors, nutritional information, and additional conditions that may affect ulcer healing. The wound journal also contains a follow-up part where the PU and recommended treatment measures, including cushions, mattresses, pressure relief, and positioning, are continuously registered at every wound session. The wound journal was used during the feasibility study, and necessary changes were done, based on feed-back from the interdisciplinary wound team at the hospitals, and the participating patients. The questionnaire forms and time lapse of the RCT are shown in Table 1.

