## Background

In 2016, 126 persons in Norway were admitted to hospital for specialized rehabilitation after a newly acquired spinal cord injury (SCI) [1]. SCI has a huge impact on the individual, the family, and the health care system. People suffering from SCI are at particular risk of developing pressure ulcers (PUs) due to paralysis, reduced skin sensitivity, and skin exposure to moisture for extended periods of time [2]. Travelling long distances can worsen the condition or even cause new ulcers to develop [3–6]. In addition to direct treatment-related costs, PUs also have a significant impact on patient morbidity, mortality, and quality of life (QoL) [3, 7–9]. The actual number of persons with SCIs and PUs in Norway is unknown. We currently do not know the reasons that individuals develop PUs, and the best follow-up in those with SCI who develop a PU.

A narrative review concerning the use of telemedicine in the group of persons with SCI (teleSCI) for the last 20 years demonstrated many benefits, such as a high level of satisfaction, environmental favorability, and positive health-related cost-beneficial outcomes [10]. A previous feasibility study evaluated telemedicine as a possible alternative method for follow-up in the group of persons with SCI and PU [11]. Cost-benefit analysis of this feasibility study indicated that teleSCI provides savings for public health services, and that using telemedicine in other patient groups with similar problems could be beneficial [11]. This is in line with other studies demonstrating that telemedicine will reduce costs [12–14].

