### Hypotheses

Epidemiological knowledge of persons with SCI and PUs will provide insight of this complicationCompared to other methods, PU treatment and healing will be more optimal by using teleSCI for follow-up at home measured in terms of healing, user interaction, and satisfaction

TeleSCI allows specialized hospital-based interdisciplinary teams to offer safe and effective treatment at home for persons with SCI and PUteleSCI enables specialized interdisciplinary health care workers to interact with, and empower, the primary health care workersOutpatient follow-up via teleSCI will shorten the time used for medical consultations when assessing PUOutpatient treatment via teleSCI will save money and time, compared with traditional treatment in hospital

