### The teleSCI group

The participants with SCI and PU (*n* = 30) and their local caregivers will be offered interdisciplinary outpatient follow-up every second or third week, provided by the specialized SCI department’s wound team via videoconferencing. The follow-up will consist of teleSCI appointments, visits to the SCI outpatient wound clinic at the hospital and telephone consultations. The Template for Intervention Description and Replication (TIDieR) [31] Checklist and Guide (Table 2) has been used to record and describe the intervention by teleSCI. This will secure treatment fidelity, replication for future trials, and transparency of reporting the results.

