### The usual care group

The participants with SCIs and PUs (*n* = 30) and their local caregivers will receive guidance based on existing routines provided by the specialized SCI department’s wound team. Telephone contact and appointments at the SCI outpatient wound clinic will be based on initiative taken by the local health care service/patient/next of kin. As usual, as care services vary in type and frequency, the follow-up provided for each participant will depend on the local resources available.

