### Fidelity

For each participant in both groups of the RCT, an interdisciplinary wound journal with questions concerning whether treatment is in adherence with the planned evidence-based treatment guidelines will be made for each consultation. The standardized report contains questions in accordance with the planned protocol, and will be used by the research investigator to ensure the fidelity of the project. A report will be sent to the participant and their general practitioner after each consultation. All forms have been created before the start of the study.

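### Adverse events and worsening go into a journal completed at consultations, whose frequency is set by arm, so a between-arm comparison of events without admission is open to ascertainment bias

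*Protocol article*

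**What the plan says.** The commitment is in the Intervention section: "All adverse events and worsening of the condition will be recorded in the wound journal and in the report form".

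- **When the journal is completed.** Table 1 lists the Interdisciplinary Wound Journal at each consultation. The Fidelity section says that, for participants in both groups, "an interdisciplinary wound journal with questions concerning whether treatment is in adherence with the planned evidence-based treatment guidelines will be made for each consultation". The Intervention section says that the ulcer and the recommended measures "are continuously registered at every wound session".
- **Contact in teleSCI.** Participants "will be offered interdisciplinary outpatient follow-up every second or third week"; Table 2 continues this until healing or for at most 52 weeks.
- **Contact in usual care.** Telephone contact and clinic appointments "will be based on initiative taken by the local health care service/patient/next of kin". The Participants section (Study 2) likewise describes follow-up on request.
- **Adverse events in general.** The Adverse events section says they "will be collected, assessed, and reported in accordance with Norwegian legislation" and will appear in the trial outcomes. It gives no timing or method of enquiry for either arm.
- **Admissions.** The Drop outs section has length and cause of hospital admission registered, without distinction by arm.
- **Safety as a hypothesis.** The Hypotheses section states: "TeleSCI allows specialized hospital-based interdisciplinary teams to offer safe and effective treatment at home".

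**The concern.** How often harm can be entered in the journal depends on the allocated arm. The wound team looks at a teleSCI ulcer on a fixed short cycle. In usual care it learns of an infection, a deterioration or a new ulcer only if someone makes contact. The promise to record *all* events cannot be kept equally well in both arms, and the shortfall is likelier in usual care, especially for milder or passing events.

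The events are to be reported with the trial outcomes, where readers will compare the arms. With equal true risks, teleSCI could appear to cause more harm simply because it is observed more closely. The same mechanism could hide a real reduction in harm under teleSCI.

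**Working it through.** **1. Recording occasions.** From Table 2 and the teleSCI section, a participant whose ulcer stays unhealed has 52/3 = 17.3 to 52/2 = 26 scheduled contacts, so about 17 to 26. In usual care the article fixes none between baseline and the 12-month/conclusion assessment.

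**2. Other routes by which harm could be recorded.**
- The report form named beside the journal has no stated timing. The Fidelity section describes a report sent after each consultation, but it is only an inference that this is the same document.
- Table 1, which summarises the forms, lists no separate adverse-event form.
- The Adverse events section sets a duty that applies to both arms, but no method that would equalise them.
- Admissions are registered separately. This is the one harms-related item described that is not tied to a consultation.

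**3. Figures in the plan.** There is none for harms. The only planning figure is the sample size: 2 × (1.960 + 0.842)² / 0.8² = 24.53, so 25 per group at two-sided 5% (assumed, as the article states no level) and 80% power. It reproduces and is not in dispute; only the planned 30 per group is used below.

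**4. Illustration of size.** The article gives no event rates and no detection rates, so both are assumed. Let the true proportion with an event be p in both arms, with full detection in teleSCI and detection d in usual care. Recorded proportions are p and p × d, and the recorded risk ratio is p/(p × d) = 1/d. The last two columns enumerate all outcomes exactly for 30 per arm, using the uncorrected chi-square test at two-sided 5%. They give the chance of a significant excess in teleSCI when there is no true difference (nominal 2.5% in that direction).

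| d | Recorded at p = 40% (teleSCI vs usual care) | Recorded risk ratio | False excess, p = 40% | False excess, p from 20% to 60% |
|---|---|---|---|---|
| 1.00 | 40% vs 40% | 1.00 | 2.4% | 2.4% |
| 0.90 | 40% vs 36% | 1.11 | 4.9% | 3.8% to 6.8% |
| 0.75 | 40% vs 30% | 1.33 | 12.1% | 7.2% to 21.7% |
| 0.50 | 40% vs 20% | 2.00 | 39.2% | 19.3% to 66.3% |

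**5. A hidden benefit.** Suppose the true risks are 30% in teleSCI and 50% in usual care, with d = 0.6. Usual care is recorded as 0.50 × 0.6 = 30%, so the table shows 30% vs 30% and the difference disappears.

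**The case against.** The strongest reply is that usual-care contact is made on request, so worsening may itself bring about the contact at which it is recorded. Contact can be started by the local service or next of kin as well as the patient, and the Intervention section carries the principle of a few dedicated home-care nurses into both arms. This stands. It means that under-recording in usual care is probable rather than established, and that the excess could be nil.

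Several stronger readings are tempting, and the article does not support them:

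- *Usual-care harms depend on patient self-report.* They do not depend on it alone, for the reason just given. The Background says these patients are at risk of ulcers "due to paralysis, reduced skin sensitivity, and skin exposure to moisture for extended periods of time", which explains why ulcers develop. It does not say that deterioration of a known ulcer under local care goes unnoticed.
- *The journal is the only source of safety data.* Admissions are registered separately, and the report form's timing is not stated.
- *The safety hypothesis cannot be tested.* The Hypotheses section names no comparator or margin for safety. Harms in the closely observed teleSCI arm can be described and admissions can be compared. A bias that makes teleSCI look worse also cannot falsely support its safety.
- *The excess is three- to four-fold.* Dividing an assumed 3-week episode by an assumed 8- to 12-week contact interval gives 38% to 25% detection, hence ratios of 2.7 to 4. That requires contact timing to be unrelated to episodes, which contact on request contradicts.
- *A safety endpoint is missing.* A condensed article may leave this, and the detailed collection schedule, to the full protocol or analysis plan.

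What remains is that the stated recording rule is itself unequal by arm, and that nothing described offsets this for events managed outside hospital.

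**Conclusion.** The point holds in limited form. A between-arm comparison of infections, worsening and other events without admission is open to ascertainment bias, probably against teleSCI. Description of harms within teleSCI and comparison of admissions remain possible.

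The size cannot be derived from the article. On the assumption that usual care detects 50% to 90% of what teleSCI detects, equal true risks appear as a recorded risk ratio of 2.0 to 1.11, and the ratio is 1 if every episode prompts a contact. The chances of a false significant excess depend further on the assumed true event proportion and on the planned 30 per arm.

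**What to change.** 1. **Comparison.** Base any between-arm safety comparison on events that depend less on wound-team contact: pressure-ulcer admission and surgery, from the registration in the Drop outs section and the hospital journals, and death. Count them from randomisation in both arms, and report the difference with its 95% confidence interval. They depend less on contact but are not independent of it, because the Intervention section lets the team recommend surgery or inpatient care.
2. **Common enquiry.** Add one identical adverse-event checklist (treated infection, new pressure ulcer) at the existing 12-month/conclusion assessment for participants who have not finished. Use a hospital-journal look-up for those who have. Trial status gives about 50 recruited and nearly 40% finished, so about 0.4 × 50 = 20 could no longer complete the checklist; if 60 are recruited, about 60 − 20 = 40 could.
3. **Journal events.** List them descriptively only, beside the number of contacts per participant, which Secondary endpoints already has recorded.
4. **Wording.** In the Intervention section, limit *all* to events known to the wound team.

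The cost is one short form at an existing assessment, a journal look-up for up to 60 participants and one table. No usual-care contact is added, so the contrast between arms is untouched. The drawbacks are recall error, which may differ by arm because a report follows each consultation and teleSCI participants are likely to receive more of them, and incomplete capture of events treated only by municipal services.

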### The teleSCI group

The participants with SCI and PU (*n* = 30) and their local caregivers will be offered interdisciplinary outpatient follow-up every second or third week, provided by the specialized SCI department’s wound team via videoconferencing. The follow-up will consist of teleSCI appointments, visits to the SCI outpatient wound clinic at the hospital and telephone consultations. The Template for Intervention Description and Replication (TIDieR) [31] Checklist and Guide (Table 2) has been used to record and describe the intervention by teleSCI. This will secure treatment fidelity, replication for future trials, and transparency of reporting the results.

### The usual care group

The participants with SCIs and PUs (*n* = 30) and their local caregivers will receive guidance based on existing routines provided by the specialized SCI department’s wound team. Telephone contact and appointments at the SCI outpatient wound clinic will be based on initiative taken by the local health care service/patient/next of kin. As usual, as care services vary in type and frequency, the follow-up provided for each participant will depend on the local resources available.

### Fidelity

For each participant in both groups of the RCT, an interdisciplinary wound journal with questions concerning whether treatment is in adherence with the planned evidence-based treatment guidelines will be made for each consultation. The standardized report contains questions in accordance with the planned protocol, and will be used by the research investigator to ensure the fidelity of the project. A report will be sent to the participant and their general practitioner after each consultation. All forms have been created before the start of the study.

### Technical solutions [32]

In this project, we use the term “teleSCI” about computer-based videoconferencing with remote webcam and the use of telephones [33–35].

The technical solution is in line with the “Sunnaas model of telerehabilitation” [36, 37], with has also been used in other research projects concerning telerehabilitation at Sunnaas Rehabilitation Hospital [11, 32]. Based on the experiences from these projects, videoconferencing guidelines have been established at the hospital [33–35].

We will use Cisco Meeting/Acano videoconference software, and videoconferencing equipment installed at the outpatient clinic at the SCI departments at Haukeland University Hospital and at Sunnaas Rehabilitation Hospital. Participants will be given a webcam for the duration of the project. The camera will be connected to either the participant’s laptop or to a project laptop, containing downloaded, encrypted videoconferencing software (Cisco Meeting/Acano) delivered by the Norwegian Health Net (NHN). This is a company owned by the Ministry of Health and Care services in Norway. The encrypted software meets requirements with regards to data safety aspects, privacy, and confidentiality [19]. As the therapy sessions are live, there are no recordings or storage of video, sound or picture. The project wound nurse and a technician will be available to support and assist the participants should technical problems arise.

Our current technical setup builds upon experience from the feasibility study [11]. To maintain safety aspects, a checklist has been implemented to be used at the start of each therapy session to control and adjust the patient’s physical environment [34]. This is to ensure optimal follow-up conditions, preserve accurate procedures in case of emergency and to accommodate privacy issues. Technical errors will be logged in each consultation.

### Sample size

For the demonstration of effect between the two groups, sample size calculation is based on an expectation of a standardized difference of at least 0.8 (typically considered a large effect). With 80% power, we will need 25 participants in each of the two groups hence we include 30 in each group to tolerate some drop outs.

### Statistical analysis

Data from the end of the study will be analyzed using chi-square tests for categorical data and *t* tests for continuous data. Regression analyses (linear and logistic) will be performed to make any necessary adjustments for baseline differences. In addition, we will also analyze developments over time in the two groups, using the mixed-models analysis.

Mean QoL scores with corresponding 95% confidence interval will be estimated in each of the two treatment groups, and the groups will then be compared using *t* tests and mixed-models analysis. A cost-benefit analysis will be carried out to assess the cost of outpatient treatment via telemedicine, compared with outpatient treatment at the hospital.

The reduction (in percentage) of PU size is calculated with corresponding 95% confidence interval for each of the two treatment groups. The groups will be compared with regard to percentage reduction in ulcer size, using *t* tests and mixed models. All quantitative statistical analyses will be performed using the SPSS and STATA statistical software package. Computer Assisted Qualitative Data Analysis (CAQDAs) will be used in the qualitative analysis.

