##### Primary endpoints

Study 2 will focus on the effect of using teleSCI compared with other outpatient approaches in the follow-up of persons with PUs after a SCI, measured in terms of percentage wound size healed, and the time to heal. A systematic evaluation of the ulcer will be done, using the validated Time Infection Moisture Edge (TIME) form [26] and the Photographic Wound Assessment Tool (PWAT) scale [27], where the amount of fibrin and granulation tissue present, percentage of epithelialization of the wound, percentage of moisture present, and the appearance of the wound edges will be described. Time to heal will be measured counting days until healing, or measuring the amount of healing at the end of the 12-month follow-up period. Changes in self-reported health-related quality of life (HRQoL) and the need for assistance will be compared using the 12-item Short Form Health Survey (SF-12v) [28], the Five Dimensions European Quality of Life scale (EQ-5D) [23], and the International Spinal Cord Injury Quality of Life questionnaire (ISCI-QoL) basic data set [29]. The SF-12v [28] measures functional health and well-being from the patient’s point of view. The EQ-5D scale [23] measures mobility, self-care, activities, pain, discomfort, and anxiety/depression. The participants perform a self-rating of their health in a box-scale and on a vertical visual analog scale. In the ISCI-QoL questionnaire [29], the participants will rate their physical and psychological health, using a box-scale. The SF-12v [28], EQ-5D [23], and ISCI-QoL [29] will be used as a quantitative measure of the health outcome that reflects the participant’s own health judgment before and, at the end of, the follow-up period. The Spinal Cord Independence Measure, version III (SCIM III) scale [24] has been designed specifically for persons with SCI and is a comprehensive ability-grading scale, focusing on the ability of performing basic tasks, and the effect the SCI has on the overall medical condition and comfort. SCIM III [24] will be rated at baseline and at the end of the follow-up period, and the results from both groups in the RCT will be compared with focus on changes in performing ability during the follow-up period.

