##### Secondary endpoints

The health care services as well as patient satisfaction and participation in both groups will be measured and evaluated using customized questionnaires.

In the cost-benefit form we will ask for time used at each consultation, travel distance to drive to and from the outpatient clinic at the SCI departments, as well as time used to travel, and distance driven for the local caregivers to and from the participants’ home. The number of caregivers participating in each session will be recorded, together with the total number of consultations for each participant, including teleSCI consultations, outpatient appointments at the hospital and telephone calls. Loss of working time for the participant and for any caregivers will be recorded, and so will medication and bandages used in every treatment session, both at the hospital and at home. CO_2_ emissions and costs for the environment will be mapped at every session.

Any technical problems will be mapped at every session. A custom-made questionnaire about the user’s experience with the follow-up will be mapped at the end of the follow-up period. This form contains questions about sufficient information provided before the inclusion, and during the follow-up period, as well as the participants’ experience regarding the follow-up. The results from the two groups will be compared with focus on differences in the user participation and satisfaction.

The investigators at the SCI departments at Haukeland University Hospital and Sunnaas Rehabilitation Hospital will supervise the filling in of the questionnaires and forms. After the conclusion of the follow-up period, a sample of participants will be requested to participate in a semi-structured qualitative interview based on the participants’ observation and experience.

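### The only test named for categorical outcomes ignores order, so any graded satisfaction or participation item analysed as categories would lose power and could be significant without showing that one arm is better

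*Protocol article*

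**What the plan says.** The general rule for the trial's final comparison, in the Statistical analysis section, is: "Data from the end of the study will be analyzed using chi-square tests for categorical data and *t* tests for continuous data". The section adds: "Regression analyses (linear and logistic) will be performed to make any necessary adjustments for baseline differences". Mixed models are to describe change over time. QoL scores are handled separately: "the groups will then be compared using *t* tests and mixed-models analysis". Percentage reduction in ulcer size is also given *t* tests and mixed models. No rank test, trend test or ordinal regression is named anywhere in the article.

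The Hypotheses section is directional: "PU treatment and healing will be more optimal by using teleSCI for follow-up at home measured in terms of healing, user interaction, and satisfaction". Under Secondary endpoints, "patient satisfaction and participation in both groups will be measured and evaluated using customized questionnaires", and "The results from the two groups will be compared with focus on differences in the user participation and satisfaction". No test is named there, so these outcomes fall under the general rule. The article does not say whether the items are graded, how many levels they have, or whether they are summed to a score.

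**The concern.** The Pearson chi-square test for a table of two arms by k answer categories has equal category proportions as its null and any departure from that as its alternative. Shuffling the category labels leaves the p value unchanged. The hypothesis is about movement in one direction along a scale from worse to better.

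If a graded item is analysed as categories, two things follow. The test spreads its sensitivity over k−1 degrees of freedom and is weaker than a one-degree-of-freedom test against an ordered shift. It can also be significant because answers in one arm are more polarised, with no shift towards better answers. With only 25 to 30 people per arm, a true improvement in satisfaction could be missed, or a difference in spread could be read as benefit.

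**Working it through.** **Inputs from the article.** Standardized difference 0.8, 80% power, 25 needed and 30 enrolled per arm (Sample size). Alpha is not stated; two-sided 0.05 is assumed.

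**Reproducing the plan's figure.** n per arm = 2(1.960 + 0.842)²/0.8² = 24.5, so 25. The exact *t*-test calculation gives 26. The stated figure reproduces. One-sided 0.05 would give 20, which supports the two-sided assumption.

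**Assumptions.** The article ties 0.8 to no endpoint. Here it is applied as a shift of a normal latent variable behind an ordered item. The number of levels and the baseline answer distributions are assumed and varied.

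**Hand check, five even levels.** Control proportions p are 0.20 in each level. The cut points are −0.842, −0.253, 0.253 and 0.842. Moving them down by 0.8 gives intervention proportions q = 0.050, 0.096, 0.146, 0.224, 0.483.

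- Chi-square noncentrality = n Σ(p−q)²/(p+q) = n(0.0895 + 0.0367 + 0.0084 + 0.0014 + 0.1175) = 0.2535n. That is 7.60 at n = 30 and 6.34 at n = 25. Against the 4-df critical value of 9.49, power is 58% and 49%.
- Rank test: the probability that an intervention answer is better, counting ties as half, is 0.699. With the tie-corrected variance (0.00522 at n = 30, 0.00627 at n = 25), z = 0.199/√variance = 2.75 and 2.51. Power is 79% and 71%.

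The squared z values (7.58 and 6.31) almost equal the noncentralities. The rank test thus keeps nearly all the signal and spends one degree of freedom instead of four. The gap is 21 to 22 points.

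**Simulation.** 40,000 trials per cell, Pearson chi-square against the tie-corrected Wilcoxon-Mann-Whitney test, latent shift 0.8 SD. Entries are power in %, chi-square / rank test, with the loss in points in brackets.

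| Levels | Baseline % | 25 per arm | 30 per arm |
|---|---|---|---|
| 3 | even | 56.8 / 67.5 (10.8) | 65.4 / 75.2 (9.8) |
| 3 | 15/35/50 | 48.2 / 60.4 (12.2) | 57.1 / 68.6 (11.5) |
| 4 | even | 53.4 / 71.4 (17.9) | 62.2 / 78.9 (16.7) |
| 4 | 10/20/35/35 | 47.5 / 67.9 (20.4) | 57.1 / 76.0 (18.9) |
| 5 | even | 48.8 / 73.0 (24.3) | 58.7 / 80.8 (22.1) |
| 5 | 5/10/20/35/30 | 42.8 / 70.0 (27.2) | 52.1 / 77.7 (25.6) |
| 7 | even | 41.3 / 74.9 (33.6) | 51.4 / 82.4 (31.0) |
| 7 | 4/6/10/15/20/25/20 | 37.2 / 73.3 (36.1) | 46.4 / 80.7 (34.4) |

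**Smaller effects.** For five levels at 0.5 SD the loss is 16 to 20 points; at an odds ratio of 2 it is 12 to 15.

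**No difference between arms.** For five-level items, chi-square rejects in 3.3 to 4.9% of trials. At least one expected count is below 5 in 81 to 100% of five-level trials, but this does not raise the error rate.

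**Spread only, same centre.** With 5/20/50/20/5% in one arm and 20% in every level in the other, chi-square rejects in 59% (n = 25) and 69% (n = 30) of trials, against 6% for the rank test. With 10/20/40/20/10% against 20% in every level, it is 26% and 31%, against 5 to 6%.

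**Where nothing is lost.** A yes/no item has one degree of freedom under either test. On five-level scores the *t* test stays within about 5 points of the rank test.

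**The case against.** The strongest reply is that the premise is not documented. The questionnaires are described only as customized. If items are yes/no, there is no loss. If they are summed, the *t* test in the same sentence applies. Chi-square tests in the plural do not exclude a trend version, and logistic regression could include an ordinal model. The choice of test for each questionnaire item is often left to an analysis plan. These outcomes are mainly secondary, in a trial that calls itself a pilot.

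Much of this stands, and it is why the point is conditional. It does not remove the point. The article does not stay silent on the test for categorical data: it names one, and that test as ordinarily applied discards order. This is a stated choice with a better alternative rather than missing detail.

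Three stronger readings are tempting and not supported:

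- That self-rated health is affected, because in the ISCI-QoL "the participants will rate their physical and psychological health, using a box-scale". The Statistical analysis section gives QoL scores *t* tests and mixed models.
- That the TIME and PWAT components will be tested by chi-square. The article says they will be described and plans no item-by-item comparison.
- That rejecting on spread is a false positive. It is a valid rejection of equal distributions; only its interpretation as benefit fails.

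**Conclusion.** The point holds in conditional form. If graded satisfaction, participation or experience items are analysed as categories, the stated test does not match the directional hypothesis. At a latent shift of 0.8 SD with 25 to 30 per arm it costs about 10 to 12 points of power for three levels, 16 to 20 for four, 21 to 27 for five and 31 to 36 for seven. These figures rest on two-sided 0.05, assumed answer distributions, and the use of 0.8 as a latent shift. A reader might take the five-level figure as a fixed property of the test, or as a statement about this trial's questionnaire. It is neither, because the loss depends on effect size and on a number of levels that the article does not give. A significant chi-square on such an item would not by itself show that teleSCI answers are better. The comparisons of QoL scores and percentage ulcer reduction are unaffected.

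**What to change.** In the Statistical analysis section, restrict the chi-square test to binary and unordered items, with Fisher's exact test for sparse tables. State that any ordered item analysed as categories will be compared by the Wilcoxon-Mann-Whitney test or by a proportional-odds model with hospital, the randomization stratum, as covariate. Report the effect with its 95% CI: the odds ratio, or the probability that a teleSCI answer is better. If items are to be summed and compared by *t* test, saying so would settle the matter for them.

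The cost is a sentence or two. Both methods are available in the named software and no data collection changes. The small downside is that the proportional-odds estimate assumes a common shift across levels. The rank test does not need that assumption to be valid under equal distributions.
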